### Data Collection and Management

All data collected in this study will be recorded in standardized electronic case report forms (CRFs; see Multimedia Appendices 1-4). We plan to use Hermes software. Hermes is a tool developed by sponsor-investigator AS, used for a patient registry, and validated by the local ethics committee board (authorization # CERVD AO_2020-00006). Only data with logical numeric variables within the correct ranges or predefined categorical variables can be entered into the electronic CRFs. Data entry for variables of interest is mandatory.

CRFs will be kept current to reflect participant status at each phase during the course of the study. Study-related data will be collected in a coded manner (participants will not be identified in the CRF by name or initials). Identification of patients must be guaranteed at the study site. Patients’ identifications will be recorded in a sequential list stored in the local investigator’s secured server. At the end of the study, when the database has been checked for completeness and validated by the sponsor-investigator, it will be locked and used for statistical analyses. All “study essential documents” (eg, informed consent form, CRFs) will be archived for at least 10 years after completion of the clinical trial.

Data sharing is not applicable to this article, as, to date, no data sets have been generated nor analyzed.

### Statistical Analysis

The WOMAC score will be normalized to a 0%-100% scale, where 0% indicates no symptoms and 100% represents the highest severity of symptoms. This normalization involves converting the raw scores into percentages, facilitating the interpretation and comparison of results across participants and study groups. The absolute difference at 6 months will serve as the primary outcome and will be compared using either the paired Student *t* test or the Wilcoxon signed-rank test, depending on the distribution of the variable, with intention-to-treat analysis. The absolute differences in secondary outcomes (changes from baseline to other time points) between the treatment and control groups will be evaluated with the appropriate statistical test (categorical variables: chi-square or Fisher exact tests; continuous variables: Student *t* or Wilcoxon rank tests). All analyses will include both intention-to-treat and per-protocol analyses. Effect estimates, 95% CIs, and descriptive *P* values will be reported whenever possible, along with corresponding graphs.

A post hoc analysis will attempt to identify variables of interest using the appropriate global linear model.

Since the intervention is considered low risk, no interim analysis is planned. In case of missing primary outcome data, patients will be withdrawn from the analysis. Patients missing secondary outcome data will remain in the study but be excluded from those specific analyses.

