### Sample Size

The sample size for this study was calculated using PS software (Vanderbilt University) [24]. We aimed to detect a clinically meaningful difference of 9.1% in the absolute change in the WOMAC function score between the experimental and control groups. The calculation assumed an SD of 13.9%, based on findings from the study conducted by Tubach et al [25].

In their study, Tubach et al [25] evaluated changes in the WOMAC function score in patients with knee osteoarthritis treated with NSAIDs over a 4-week period. They reported an average baseline WOMAC function score of 42.8 (SD 16.1) and an absolute improvement of –11.6 (SD 13.9). These values were used to estimate the variability in absolute changes for our calculation.

With these parameters, a sample size of 108 patients (54 per group) was determined to provide 90% power to detect the specified difference at a 5% significance level using a 2-tailed test. This calculation ensures that our study is adequately powered to detect a meaningful treatment effect based on absolute improvements in functional outcomes. The study will collaborate with health care providers in both study centers to achieve the target sample size. Additionally, potential participants will be contacted through patient registries and referrals. All recruitment efforts will comply with ethical guidelines and prioritize informed consent. Figure 2 shows the CONSORT (Consolidated Standards of Reporting Trials) diagram [26].

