### Randomization and Blinding

Study participants will be randomized at a 1:1 ratio to either the intervention arm or the active comparator arm using a randomization table and blocked randomization with blocks of 4 patients. Participants will be assigned to specific strata based on age (older or younger than 40 years) and the presence of cartilage defects (partial, full, or full with bone deformation).

The unblinded investigator responsible for the study interventions will perform the randomization shortly before administering the interventions. This study is triple-blinded: (1) Participants will be unaware of their group assignment throughout the intervention and study duration, (2) the investigator performing the intraarticular injection and the outcome assessor will remain blinded, and (3) the statistician will also be blinded. The investigator responsible for preparing the PRP+SVF or PRP-only preparation will be unblinded and will not participate in outcome assessments.

All patients will undergo a venipuncture, either a lipoaspirate or a sham lipoaspirate, followed by an ultrasonographically guided PRP or PRP+SVF injection. It is anticipated that unblinding will not be required to ensure patient safety, as no known adverse effects of the SVF (such as local pain, tenderness, hematoma on donor site, or infection) require unblinding for clinical management. However, if unblinding becomes necessary due to unexpected circumstances, the unblinded investigator will disclose the allocated intervention for the affected patients.

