The meta-analysis by Lee et al [19] showed some differences between both therapies on clinical outcomes. A significant improvement in the VAS score was found at 6 months and 12 months with AD-MSCs (6 months: MD=–1.62, 95% CI –2.46 to –0.79; 12 months: MD=–1.97, 95% CI –3.22 to –0.72), whereas SVF showed significant results only at 12 months (6 months: MD=–2.32, 95% CI –5.15 to 0.52; 12 months: MD=–2.13, 95% CI –3.06 to –1.21). In contrast, functionality measured with WOMAC scores improved significantly 6 months after SVF treatment (MD=–6.12, 95% CI –10.71 to 1.52), while AD-MSC therapy yielded significant improvements only after 12 months (6 months: MD=–1.96, 95% CI –5.36 to 1.45). At 12 months and 24 months, both SVF and AD-MSC therapies produced significant improvements in the WOMAC score (12 months SVF: MD=–9.09, 95% CI –12.67 to –5.51; 12 months AD-MSC: MD=–9.19, 95% CI –12.48 to –5.90; 24 months SVF: MD=–10.71, 95% CI –18.49 to –2.93; 24 months AD-MSC: MD=–6.88, 95% CI –10.24 to –3.52).

The first main strength of our study design is the large sample size. Second, our study population is well-designed and reproducible, with standardized diagnostic criteria and failure of a first-line standardized rehabilitation plan. Third, the multicenter design allows for better reproducibility of patient selection and management, even if interventions are performed at the main study center by a single investigator. This is, however, a study strength, as it will avoid bias related to the intervention techniques.

A sham lipoaspiration procedure with the patient awake is performed to maintain blinding in the control group. Despite all precautions taken to uphold allocation concealment, breaches may occur if the patient diligently questions the procedure. For ethical reasons, if at 6 months, the progression is unsatisfactory, the intervention's nature may be disclosed if deemed clinically relevant, allowing the patient to benefit from SVF infiltration. Consequently, the study may be limited, as the initial 12-month secondary outcomes will not be considered in the final analysis. Finally, the patient selection, clinical follow-up, and rehabilitation plan might differ across the various recruitment centers (multicenter design).

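### Free improvement: the primary comparison is an unadjusted test; baseline WOMAC and the two stratification factors should be prespecified as covariates

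*Protocol article*

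**What the plan says.** Under Statistical Analysis, the protocol article says "The absolute difference at 6 months will serve as the primary outcome". It is to be compared by a paired Student t test or a Wilcoxon signed-rank test, depending on its distribution. No covariate or stratification factor is named. The only model in the section comes later: "A post hoc analysis will attempt to identify variables of interest using the appropriate global linear model".

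Randomization and Blinding describes 1:1 allocation in blocks of 4: "Participants will be assigned to specific strata based on age (older or younger than 40 years) and the presence of cartilage defects". Age has two levels and cartilage defect three, which makes six strata. Outcome Measurements and Assessments, with Table 1, shows that WOMAC is collected at baseline.

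The primary variable is not defined outright as a change from baseline, but two places point that way. Sample Size aims to "detect a clinically meaningful difference of 9.1% in the absolute change in the WOMAC function score between the experimental and control groups" and uses the SD of a change: "The calculation assumed an SD of 13.9" (percentage points). Statistical Analysis describes the secondary outcomes as changes from baseline to the other time points.

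**The concern.** The design collects a strong candidate predictor of the outcome and balances the arms on two further factors. The stated primary test uses none of the three as a covariate. Because the test is named in the text, this is a choice already made and not a detail left to an analysis plan.

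Two things follow. First, subtracting baseline fixes its coefficient at 1. When the true slope of 6-month on baseline WOMAC differs from 1, a model that estimates the slope has smaller residual variance. Second, stratified allocation removes between-stratum variation from the treatment contrast, while an unadjusted standard error still contains it. If the strata are prognostic, the test rejects too seldom and the interval is too wide.

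The sentence has a further fault that the same change would remove: paired and signed-rank tests do not compare two independent arms.

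At stake are the precision and calibration of the primary estimate.

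**Working it through.** **Inputs from Sample Size:** difference 9.1; SD of change s_c = 13.9; baseline SD s_0 = 16.1 in the cited 4-week NSAID study; 54 per arm; two-sided 5%; 90% power. **Not in the documents, so assumed:** the 6-month SD s_1, and the share R² of outcome variance explained by the strata.

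**1. The plan's own figure.** The normal formula gives n = 2(1.960 + 1.282)² × 13.9² / 9.1² = 49.03, so 50 per arm. The two-sample t calculation gives 50.01, so 51. The total is 100 to 102 against the stated 108. At 54 per arm, power is 92.1% (t) or 92.5% (normal). The stated size is slightly generous for these inputs.

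**2. Change score against ANCOVA.** Since s_c² = s_0² + s_1² − 2·r·s_0·s_1, the baseline to 6-month correlation is r = (s_0² + s_1² − s_c²)/(2·s_0·s_1). The slope is r·s_1/s_0, and the ANCOVA residual SD is s_1·√(1 − r²).

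For s_1 = 16.1:
- r = (259.21 + 259.21 − 193.21)/518.42 = 0.627, and the slope is also 0.627
- residual SD = 16.1 × √(1 − 0.627²) = 12.54
- variance ratio = 12.54²/13.9² = 0.81

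Across assumed values of s_1 (power for 9.1 points at 54 per arm; the unadjusted change score gives 92.1% throughout):

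| Assumed s_1 | r | Slope | Residual SD | Variance ratio | ANCOVA power |
|---|---|---|---|---|---|
| 13.9 | 0.579 | 0.50 | 11.33 | 0.665 | 98.5% |
| 16.1 | 0.627 | 0.63 | 12.54 | 0.81 | 96.2% |
| 18 | 0.673 | 0.75 | 13.32 | 0.92 | 94.0% |
| 20 | 0.724 | 0.90 | 13.80 | 0.99 | 92.4% |
| 21.27 | 0.757 | 1.00 | 13.90 | 1.00 | 92.1% |

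The gain vanishes where the slope is 1, at s_1² = s_0² + s_c² = 452.42, so s_1 = 21.27. The ratio equals 1 minus the squared correlation of change with baseline, so it cannot exceed 1.

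**3. Cost in degrees of freedom.** Main effects need 1 (baseline) + 1 (age) + 2 (cartilage) = 4. The table's powers use 100 residual df, which charges for all six strata plus baseline (6 extra). With no gain at all, power falls from 92.09% to 92.06%, and the critical t rises by 0.07%.

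**4. Leaving out the strata.** With near-perfect balance, the unadjusted t statistic has null SD of about √(1 − R²). By the normal approximation, the type I error is P(|Z| > 1.96/√0.9 = 2.066) = 3.9% for R² = 0.10, and P(|Z| > 1.96/√0.8 = 2.191) = 2.8% for R² = 0.20. A simulation of 8,000 trials (six equal strata, blocks of 4, independent-samples t test) gave 3.9% and 2.9%. The strata-adjusted test gave 4.8% and 4.7%. Intervals are too wide by about 1/√(1 − R²), that is 5% or 12%.

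**5. The other reading of the variable.** If the primary variable were the raw 6-month score with an assumed SD of 16.1, unadjusted power would be 82.9%, against 96.2% with ANCOVA.

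**The case against.** The strongest reply is that nothing here invalidates the trial. An unadjusted between-arm test after stratified randomisation is valid and, if anything, conservative. Power for 9.1 points already exceeds 90% at 108 patients. That stands, although the protocol states no dropout allowance and removes patients without the primary outcome. If 10% were missing (an assumption), unadjusted power would be 89.1%.

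The size of the gain is also uncertain. It depends on a 6-month SD that the documents do not give, and both source SDs come from 4 weeks of NSAID treatment. This stands too, and is why the gain is given as a range that reaches nil.

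A reader might infer several stronger points that the documents do not support:

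- *The plan ignores baseline WOMAC.* On the better-supported reading, baseline is subtracted. What is missing is its use as a covariate.
- *A change score over-corrects whenever the correlation is below 1.* The condition is a slope below 1. At a 6-month SD of 21.27 the correlation is 0.76 and there is no over-correction.
- *The Discussion's 6-month SVF estimate of 6.12 points shows that the extra power is needed.* That figure is a pooled SVF result whose scale and comparator are not stated there, whereas this trial compares PRP with and without SVF on a 0–100 scale. Its interval is also printed as crossing zero although the text calls the result significant.
- *Adjusting for strata and centre is sure to add further precision.* No figure supports this. The Discussion does concede that "the patient selection, clinical follow-up, and rehabilitation plan might differ across the various recruitment centers", but all interventions take place at the lead centre and centre is not a stratification factor. Adjusting for it is optional.

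**Conclusion.** The point holds as a free improvement, not as an error that threatens the result. The stated primary test is unadjusted although a baseline score and two stratification factors are available.

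On the change-score reading, with an assumed 6-month SD of 16.1, ANCOVA cuts the variance by about 19% and raises power for 9.1 points from 92.1% to 96.2%. Over an assumed SD of 13.9 to 21.3 the cut runs from about a third to nothing. If the strata explain 10% or 20% of outcome variance (assumed), an unadjusted independent-samples test has a true size of about 3.9% or 2.9% instead of 5%. The downside of adjusting is about 0.03 percentage points of power.

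The power figures assume the protocol's source SDs carry over to 6 months after injection, complete data in 54 per arm, and a between-arm test in place of the paired one named. The documents do not support saying that the trial is underpowered for its target or that its conclusion would be invalid for lack of adjustment.

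**What to change.** In Statistical Analysis, replace the primary-test sentence with a prespecified between-arm linear model (ANCOVA): 6-month normalised WOMAC on treatment, baseline WOMAC, age stratum and cartilage-defect stratum. Report the adjusted mean difference with its 95% CI. Keep an unadjusted independent-samples test as a supportive analysis. Centre may be added as an optional covariate, provided that this is decided in advance.

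This also removes the paired and signed-rank wording and any doubt over how baseline enters the primary analysis.

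The cost is about one sentence and 4 degrees of freedom, with no new data. The Results section describes the protocol as ready to go to the regulatory authorities, so the change can be made before approval, after which Ethics Review Approvals requires prior ethics committee consent for amendments.

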### Outcome Measurements and Assessments

The primary outcome is functional improvement measured with the 0%-100% normalized WOMAC at the 6-month follow-up, where 0% indicates complete absence of symptoms and 100% indicates maximal possible symptom severity. A clinically relevant functional improvement is a difference of 9.1 points out of 100 points.

The secondary outcomes will be clinical and radiological parameters gathered at the 1-month, 2-month, 3-month, 6-month, and 12-month follow-ups. These include a 10-point pain visual analogue scale (VAS) during maximal physical activity performed by the patient according to manageable pain and clinical recommendations, the 0%-100% normalized WOMAC [2], length of time to return to work and sports in days, adverse events (AEs), and serious adverse events (SAEs). Pain will be assessed as an AE of interest, during the intervention and 48 hours following the intervention.

The improvement in cartilage quality will be assessed at the 6-month and 12-month follow-ups (previous MRI should not be dated more than 3 months before the intervention) using 3 key MRI-based scoring systems: Area Measurement and Depth and Underlying Structures (AMADEUS) [13], Whole-Organ Magnetic Resonance Imaging Score (WORMS) [22], and Magnetic Resonance Observation of Cartilage Repair Tissue (MOCART) [23].

We initially planned to statistically assess these outcomes at 6 months and 12 months. However, assessment of these parameters at other time points might be subject to exploratory analysis.

The participant timeline is presented in Table 1. The following information will be collected at baseline: age, gender, height, weight, BMI, smoking status, comorbidities, baseline Kellgren–Lawrence grade, current and previous treatments, and posttraumatic etiology. The set of clinical and radiological scores include the VAS, WOMAC, return to work and sports in days, AMADEUS, WORMS, and MOCART.

**Table 1 table1:** Study assessments and procedures at the study visits.

Procedures	Screening^a^	Baseline	Visit 1	Visit 2	Visit 3	Visit 4	Visit 5
Timing (visit window)	–3 weeks (+3 weeks)	0	1 month (±7 days)	2 months (±7 days)	3 months (±7 days)	6 months (±7 days)	12 months (±7 days)
Informed consent	X	—^b^	—	—	—	—	—
Inclusion/exclusion criteria	X	—	—	—	—	—	—
Baseline characteristics	—	X	—	—	—	—	—
Clinical scores	—	X	X	X	X	X	X
MRI^c^	—	X	—	—	—	X	X
Randomization	—	X	—	—	—	—	—
Lipoharvesting or sham lipoharvesting	—	X	—	—	—	—	—
Intervention^d^	—	X	—	—	—	—	—

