PRP^e^ injection	—	—	X	X	—	—	—
Concomitant medication	—	X	X	X	X	X	X
AEs^f^ and SAEs^g^	—	X	X	X	X	X	X

^a^Screening and baseline visits can be performed on the same day if the patient has been given reasonable time to make a consented decision about participation in the study.

^b^—: not applicable.

^c^MRI: magnetic resonance imaging.

^d^Stromal vascular fraction+platelet-rich plasma (PRP) or PRP-only injection depending on the group.

^e^PRP: platelet-rich plasma.

^f^AEs: adverse events.

^g^SAEs: serious adverse events.

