### Oversight and Monitoring

For quality control of the study conduct and data retrieval, all study sites will have regular monitoring activities performed by appropriately trained and qualified monitors, who are outsourced by the sponsor-investigator. Monitoring activities will consist of on-site monitoring as well as remote and centralized monitoring.

The objectives of a monitoring visit are to (1) verify the informed consent form process for each monitored participant, (2) verify the prompt and accurate recording of all monitored data points and prompt reporting of all safety events, (3) compare collected data with participants’ source documents, and (4) ensure investigators comply with the protocol.

The monitors may also inspect the clinical site regulatory files to ensure that regulatory requirements and applicable guidelines (International Council for Harmonisation [ICH] Good Clinical Practice [10]) are being followed.

SAEs will be defined as any untoward medical occurrence that results in death, is life-threatening, requires inpatient hospitalization or prolongation of existing hospitalization, results in persistent or significant disability or incapacity, or in a congenital anomaly or birth defect. SAEs should be followed until resolution or stabilization. Assessment of causality will be based on the criteria listed in the ICH E2A guidelines [10], and severity will be graded based on the Common Terminology Criteria for Adverse Events Version 5 [27]. All SAEs will be reported immediately and within a maximum of 24 hours to the sponsor-investigator of the study. The sponsor-investigator will re-evaluate the SAE and return the form to the co-investigator. SAEs resulting in death will be reported via the sponsor-investigator to the Swiss Business Administration System for Ethics Committees and to the other ethics committees involved in the trial within 7 days.

Regular audits are not planned. For the purpose of on-site inspection or audit, the competent authorities or ethics committee may require access to all source documents and other study-related records. The sponsor-investigator and local investigators must ensure the availability of these documents at any time.

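### As worded, the missing-6-month-WOMAC rule can drop early leavers with adverse events from the adverse-event comparison and understate AE rates

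*Protocol article*

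**What the plan says.** The primary outcome is fixed at one visit (Outcome Measurements and Assessments): "The primary outcome is functional improvement measured with the 0%-100% normalized WOMAC at the 6-month follow-up". The same section lists the secondary outcomes, and these include "length of time to return to work and sports in days, adverse events (AEs), and serious adverse events (SAEs"). It also singles out one early safety measure: "Pain will be assessed as an AE of interest, during the intervention and 48 hours following the intervention". Table 1 schedules AE and SAE collection at baseline and at all five follow-up visits.

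Three sentences under Statistical Analysis decide who is analysed:

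- Analysis sets: "All analyses will include both intention-to-treat and per-protocol analyses".
- Missing primary outcome: "In case of missing primary outcome data, patients will be withdrawn from the analysis".
- Missing secondary outcome: "Patients missing secondary outcome data will remain in the study but be excluded from those specific analyses".

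The section makes no exception for AEs or SAEs in any of the three. Separately, Oversight and Monitoring sets the reporting duty: "All SAEs will be reported immediately and within a maximum of 24 hours to the sponsor-investigator of the study".

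**The concern.** The two missing-data sentences stand next to each other and are worded differently. For a missing secondary outcome, the loss is confined to the analysis concerned and the patient stays in the study. For a missing primary outcome there is no such limit. A statistician applying the text would have good reason to take a patient without a 6-month WOMAC out of the dataset altogether, AE tables included.

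For efficacy this is a familiar complete-case rule. For safety it is a different matter, because the reason for having no 6-month WOMAC may be the harm itself. Events that were observed and recorded, including pain in the first 48 hours, would be left out because a questionnaire was not completed months later. The Discussion says that the extra resources SVF needs should be spent only if clear benefits are shown. That judgement also needs AE rates that count every treated patient.

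**Working it through.** **Step 1. The sentences side by side.**

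| Patient lacks | Stated consequence | Limited to the outcome concerned? |
|---|---|---|
| Secondary outcome | Stays in the study, leaves those analyses | Yes |
| 6-month WOMAC | Withdrawn from the analysis | Not stated |

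AEs and SAEs are secondary outcomes, so nothing in the text keeps them out of the second row. Take a patient with a complication at month 1 who leaves at month 2. The AE data were collected at baseline and month 1, but the 6-month WOMAC is missing. On the broad reading this patient leaves the AE comparison. An intention-to-treat analysis, which the section promises for all analyses, would keep the patient. The two statements cannot both be followed.

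**Step 2. What the broad reading does to an AE rate.** The plan gives no AE rate and no dropout rate, so there is no figure of its own to reproduce and every rate below is an assumption. Let p be the AE risk in an arm, d the proportion of patients with an AE who leave before 6 months, and d0 the same proportion among patients without an AE. The rate seen in patients with a 6-month WOMAC is

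reported rate = p(1 − d) / [p(1 − d) + (1 − p)(1 − d0)].

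With p = 10%, d = 30%, d0 = 5%:

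0.10 × 0.70 / (0.10 × 0.70 + 0.90 × 0.95) = 0.070 / 0.925 = 7.6%.

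With the planned 54 patients per group, that removes 54 × 0.10 × 0.30 = 1.6 patients with an AE from an arm, on average.

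**Step 3. What it does to the comparison.** Differences are SVF+PRP minus PRP, in percentage points.

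| AE risk, SVF+PRP / PRP | Exit with AE, SVF+PRP / PRP | Exit without AE | Reported rates | True difference | Reported difference |
|---|---|---|---|---|---|
| 10% / 10% | 30% / 30% | 5% | 7.6% / 7.6% | 0 | 0 |
| 15% / 5% | 30% / 30% | 5% | 11.5% / 3.7% | 10.0 | 7.8 |
| 15% / 5% | 50% / 50% | 5% | 8.5% / 2.7% | 10.0 | 5.8 |
| 10% / 10% | 50% / 10% | 5% | 5.5% / 9.5% | 0 | −4.0 |
| 10% / 10% | 10% / 50% | 5% | 9.5% / 5.5% | 0 | +4.0 |
| 15% / 5% | 5% / 5% | 5% | 15.0% / 5.0% | 10.0 | 10.0 |
| 15% / 5% | 0% / 0% | 20% | 18.1% / 6.2% | 10.0 | 11.9 |

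The rates are understated whenever patients with an AE leave more often than the others (d > d0). They are unchanged when leaving is unrelated to AEs, and overstated in the reverse case. The between-arm difference can shrink, stay the same, grow or change sign. Counting events in all treated patients up to last contact removes the distortion caused by the exclusion in every row.

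**Step 4. Small counts.** Suppose 3 of 54 patients in an arm have an event (5.6%). If one of them leaves and is dropped, the report is 2/53 = 3.8%. If two leave, it is 1/52 = 1.9%.

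**The case against.** The strongest reply is that the sentence can be read outcome by outcome: no primary outcome, out of the primary analysis; no secondary outcome, out of that secondary analysis. On that reading AEs are untouched. The promise of intention-to-treat for all analyses supports it, and so does the fact that an early leaver's AEs are observed data, not missing data. This reading is possible and the text does not exclude it. It is the less natural one, because only the second sentence states a limit. Nor does the section say that events recorded before exit still count.

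A second reply is that a safety population is commonly defined in a statistical analysis plan, which is not shown. That is right, and the absence of a named safety set is not the point here. The point is a stated rule that a later plan would have to narrow or override.

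Third, SAE reporting within 24 hours is unaffected on any reading. That stands. It concerns the reporting of individual cases, however, and not the comparison between arms; non-serious events are outside it.

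A reader might go further and infer that the plan makes SVF look safer than it is. The documents do not support this. It would require AE-related exit that differs between the arms, or more AEs with SVF together with AE-related exit, and no such data are given. Controls also undergo incisions, tumescent solution, sham cannula movement and joint injection. A reader might also infer that the per-protocol analysis removes patients who stopped injections because of an AE. The article does not define the per-protocol set, and it accompanies the intention-to-treat analysis without replacing it.

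**Conclusion.** Wrong as written, and minor. On its natural reading, the rule for a missing 6-month WOMAC removes early leavers from the AE comparison along with the efficacy analysis, against the intention-to-treat commitment in the same section. If patients with an AE leave more often than others, AE rates in either arm are understated; in the assumed example, 10% is reported as 7.6%. The size rests wholly on assumed AE and exit rates.

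The conclusion does not extend to a claim that the comparison favours SVF. With equal AE risk and equal exit the between-arm bias is zero, and with unequal exit it can run either way (−4.0 or +4.0 points in the examples). Nor is it established that the authors intend to exclude these patients. The finding is that the wording allows it and, read naturally, requires it.

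**What to change.** Under Statistical Analysis:

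1. Limit the missing-primary-outcome rule to the primary WOMAC analysis.
2. State that AEs and SAEs are summarised in all patients in whom the lipoharvest or sham procedure was started, counting every event up to last contact whether or not a 6-month WOMAC exists. Any per-protocol summary of AEs is supplementary only.

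The cost is about two sentences of wording. AEs and SAEs are already scheduled for collection from baseline at every visit, so no extra data, visits or patients are needed. The change is easiest now: the Results section says this version is ready to go to the Swiss authorities, and under Ethical Considerations changes after approval generally need prior ethics committee approval.
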